### Statistical analyses

All analysis are by intention to treat with a beta level of 0.10 and an alpha level of 0.025 (Type I and Type II error). The primary outcome is the percent change in the volume of the hematoma measured by a CT scan at 24 ± 3 h after the onset compared with the baseline CT scan. The volumes of the hematoma measured by a CT scan will be analyzed using generalized linear mixed models. The subjects and the readers (two neuroradiologists) will be defined as random effects, and the baseline volume of hematoma, the time from the onset to CT scanning, and the time from CT scanning to study intervention will be defined as fixed-effect covariates. The percentages of changes in the volume of hematoma are transformed to normality and eliminate negative values via logarithmic transformations. Comparisons will be made between the two treatment groups with placebo using Bonferroni’s method with a threshold of significance of 0.0167. The threshold of significance for all other comparisons was 0.05. Subjects died before finishing the follow up will be assigned the worst possible scores for measures of neurologic deficit and function prognosis. Regarding surviving subjects with missing outcome data, the last visit will be carried down. The scores on mRS will be analyzed in a cumulative logit model, with statistical adjustment for age, the baseline hematoma volume, the site of hemorrhage, and the baseline neurological status. The scores on the BI and NIHSS will be analyzed with Wilcoxon rank-sum tests. The difference of the frequency of SAE in the three groups at 3 months will be analyzed with Fisher’s exact test or the Chi square test. All dates will be analyzed via SPSS software, version 21.0.

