**Methods/design:**

A multicenter, three-group, prospective, randomized, double-blinded and placebo-controlled clinical trial. Patients aged 18 or older with HICH confirmed by CT scan within 6 h from the onset are included. 360 patients will be randomized to 3 groups (PBC & RBS & Placebo) within 6 h of ictus. Stratified block randomization is undertaken using a sequentially numbered and opaque envelope. All subjects must take medicine within 6 h of ictus and have another CT scan at about 24 h to confirm hematoma expansion. A postal questionnaire to the patients to evaluate their recorvery at 3 months. Primary outcome is the percent change in the volume of hematoma at 24 h. Secondary outcomes include: mortality, disability, serious adverse events, etc.

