### Randomization

We define the herbal medicine as PBC or RBS under the criteria of Chinese Pharmacopoeia of 2010 version. The combined herbal drugs, such as relieving heat and calming liver Yang, decreasing wind and dispersing phlegm, loosing the bowels, are also under the criteria of Chinese Pharmacopoeia of 2010 version. Within 6 h from the onset, participants will be assigned at random to one of three treatment groups with a ratio of 1:1:1: (1) Group A: RBS, stasis-breaking herbal medicine (8 herbals); (2) Group B: PBC, herbal medicine without stasis-breaking herbal medicine (6 herbals) and (3) Group C: placebo comparator, only placebo. Randomization is generated and stratified in blocks of six by PROC PLAN process using the SAS software version 9.13. Stratified block randomization is concealed using a sequentially numbered and opaque envelope. The number of each group will be in balance within research centers and by the baseline NIHSS severity (≤17 vs. >17), age (>18 years) and hemorrhagic location (basal ganglia vs. all other), patients’ sex, baseline Glasgow Coma Scale, duration from onset to the first CT scan.

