## Statistical considerations

### Sample size

The primary efficacy outcome is the percent change in the volume of hematoma at the 24th hour after onset in the two treatment groups as compared with the placebo group, assessed via the blinded measurement of hematoma by ABC/2 Coniglobus formula. The statistical hypothesis on the percentage of hematoma expansion is that the relative hematoma volume in subjects of three groups are the same to each other. Power and sample size are determined using relative hematoma volume at 24 h as the main outcome variable. According to the previous literature (Huang et al. 2010; Wang et al. 2013; He et al. 2002), the true proportions of subjects in 3 groups with different rations of hematoma expansion at 24 h are presented in Table 4. In this case, the $$\upgamma$$ is 12.65, $$\uppi\_\hbox{max}$$ 38 % and $$\uppi\_\hbox{min}$$ 7 %. With a two-sided alpha level at 0.05, 285 participants finishing the final follow up provide 90 % power to test the hypothesis of the study’s primary effectiveness, which is calculated by the following formula; assuming that the non-investigation rate of the primary outcomes is 20 %, 360 participants will be needed.

**Table 4 Tab4:** Hypothesized true outcomes for sample size calculations

Randomized group	PBC	RBS	Placebo
Percentage of change	7	16	38

*RBS* removing blood stasis, *PBC* promoting blood circulation

$$n = 1641.6\upgamma/((\sin^{ \wedge } ( - 1)\surd (\uppi\_\hbox{max} )) - \sin^{ \wedge } ( - 1)\surd\uppi\_{\rm min}^{ \wedge } 2$$

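### The primary model omits six of the seven factors on which the groups are said to be balanced, and adjusts for a time that is only completed after randomisation

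*Protocol article*

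**What the plan says.** Randomization section of the protocol article: "Randomization is generated and stratified in blocks of six", followed by a claim of balance: "The number of each group will be in balance within research centers and by the baseline NIHSS severity" (cut at 17), then "age (>18 years) and hemorrhagic location (basal ganglia vs. all other"), then sex, baseline GCS and the time from onset to the first CT. That makes seven factors. GCS and time carry no cut-points. Centre eligibility gives 13 centres, and the Abstract gives the size: "360 patients will be randomized to 3 groups (PBC & RBS & Placebo) within 6 h of ictus".

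Statistical analyses section: the primary model has random effects for subject and reader, and as fixed covariates "the baseline volume of hematoma, the time from the onset to CT scanning, and the time from CT scanning to study intervention". All analyses are declared to be by intention to treat. The mRS model in the same section adjusts for age, baseline volume, haemorrhage site and baseline neurological status.

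CT scanning section: the baseline CT is done at screening. Table 1: patients are eligible from 18 years. The section on missing data deals with missing outcomes and gives no rule for a missing covariate.

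**The concern.** Factors chosen for balance at randomisation are normally carried into the primary model. If they are left out, variation they explain stays in the error term, and an analysis that ignores the balancing tends to overstate the standard error. Here the protocol names the factors and collects them, and it uses age, site and neurological status in the mRS model but not in the primary one.

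The model instead takes in an interval that ends at first dose, after randomisation. A patient who is randomised but never dosed has no value for it. With ordinary model fitting that patient is dropped, which conflicts with intention to treat.

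The balancing claim is also weaker than it reads. One factor has in effect a single level, and crossing the others gives strata smaller than the block size.

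**Working it through.** **Inputs.** 360 patients, 3 arms at 1:1:1, blocks of six, 13 centres. Two levels each for NIHSS and location (stated) and for sex. Age has one effective level. The plan states no number of strata and no expected imbalance, so there is no figure of its own to reproduce on this point. The 360 follows from 285 completers and 20% loss: 285/0.8 = 356.25, rounded up to 357. The 285 itself does not follow from the plan's formula (41 per group, 123 in total), but that is a separate matter and nothing here uses it.

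**1. Factor list against model.**

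| Balancing factor | In primary model? |
|---|---|
| Centre | No |
| NIHSS | No |
| Age | No |
| Haemorrhage location | No |
| Sex | No |
| GCS | No |
| Onset-to-first-CT time | Yes |

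Six of seven are missing. Baseline volume is a sound addition and no fault.

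**2. Timing of the third covariate.** The order is baseline CT at screening, then randomisation, then first dose. The interval from CT to intervention therefore spans randomisation and is undefined without a dose.

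**3. Strata.** Centre × NIHSS × location × sex = 13 × 2 × 2 × 2 = 104. Patients per stratum = 360/104 = 3.5, below the block size of 6. For comparison, centre × NIHSS = 26 strata, and 360/26 = 13.8 each.

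**4. Balance delivered.** Simulated permuted blocks of six, 360 patients, centres of equal expected size, about 1,500 runs per stratified scheme. The gap is largest arm minus smallest arm.

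| Scheme | Mean gap |
|---|---|
| Centre only (13 strata) | 3.7 |
| Centre × NIHSS (26) | about 5 |
| 104 strata | about 11 (10.6 to 11.7 across runs and assumed factor prevalences) |
| Simple randomisation | 18.6 |

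With 104 strata about 92% of occupied strata end in an incomplete block and about 24% of patients sit in a completed one. The scheme lies between good stratification and none.

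**5. What the arm gap itself costs.** For two arms differing by 11, such as 125.5 and 114.5, the variance ratio against 120 and 120 is (1/125.5 + 1/114.5)/(2/120) = 1.002. Unequal arm size is therefore no material harm; the gap only shows how far the blocks do their work.

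**6. Precision.** If the omitted factors explain a share R² of the variance left after the present covariates, the standard error is multiplied by √(1 − R²). The document gives no R², so these values are assumptions.

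| R² (assumed) | SE multiplier | Reduction in SE |
|---|---|---|
| 0 | 1 | 0% |
| 0.10 | 0.949 | 5% |
| 0.20 | 0.894 | 11% |

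**The case against.** Several objections have force.

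- **The design is not fully stated.** The article does not say that all seven factors are crossed strata, and a condensed article may leave the cut-points to the full protocol. A reader might infer 416 strata (0.87 patients each) and conclude that the scheme is almost simple randomisation. That needs two levels each for GCS and time, which the article does not give. At 104 strata the mean gap is about 11 against 18.6, so the inference fails. Even 104 assumes that the four factors are crossed.
- **Omission does not bias.** Chance imbalance under valid randomisation leaves the comparison unbiased. This stands; the cost is efficiency.
- **The gain may be small.** Baseline volume and onset-to-CT time are already in the model, and NIHSS and GCS probably overlap with volume. The Background names sex, age and time window among the reasons for enlargement, but not NIHSS, GCS or location. A reader might turn R² of 0.10 to 0.20 into a gain worth 11% to 25% more patients (1/0.9 and 1/0.8). The document gives no basis for that range, and zero cannot be excluded.
- **A different outcome may need different covariates.** The mRS model concerns 90-day function, so the contrast with it only shows that the data are at hand.
- **Time to first dose is hardly affected by allocation.** Under double blinding no drug has acted by then, and dosing within 6 h is required, so undosed patients should be few. The bias risk is therefore small. What remains is that the value is undefined for such a patient and no stated rule covers it.

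**Conclusion.** The point holds as a mismatch between design and primary analysis. Six of the seven balancing factors are absent from the model, one of its three fixed covariates is completed after randomisation and is undefined for undosed patients, and the age factor separates essentially nobody. If centre, NIHSS, location and sex are the crossed factors, balance is only partly delivered.

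The consequence is lost precision and conservative standard errors. The documents do not support a claim that the treatment comparison is biased, or that the randomisation has failed. The reduction in standard error is 0% to 11% over the assumed R² of 0 to 0.20; where in that range the trial lies cannot be settled from the article. The change is worth making because the extra covariates are baseline data already collected.

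**What to change.** Before unblinding, amend the Statistical analyses section so that the primary model:

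1. adds centre as a random effect and, as fixed effects, the baseline factors used in the randomisation: NIHSS or GCS (both only if their overlap causes no trouble), haemorrhage location, age and sex;
2. keeps baseline volume and onset-to-CT time;
3. replaces time from CT to intervention by time from CT to randomisation, which exists for every randomised patient with a baseline CT.

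In the Randomization section, remove age above 18 years as a balancing factor, or state the cut-point actually used.

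Leave the randomisation scheme alone. The Discussion reports 280 of 360 patients recruited, so new strata could reach at most 360 − 280 = 80 patients and would need new lists and envelopes at 13 centres for little return.

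The cost is a short amendment to the wording and a few covariates already on the case record; the only added item is the time of randomisation, if it is not yet recorded.

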## Background

HICH is one of the most devastating forms of stroke which is a main cause of death and disability around the world (Roach et al. 2005), playing a significant part in morbidity and mortality worldwide (Qureshi et al. 2009). The proportion of patients with ICH who died within 30 days has risen to nearly 40 %, and most of the survivors cannot make a full recovery (Qureshi et al. 2009; van Asch et al. 2010). Approximately two-third of ICH patients suffer hematoma enlargement within 24 h of ictus (Lim et al. 2008). Moreover, hematoma growth is an independent prognostic determinant (Davis et al. 2006). Several reasons may be related to the hematoma enlargement in the early stage of ICH, including high blood pressure, “spot” sign of CT scan, sex, age, time window, anticoagulation drugs (Lim et al. 2008). But so far there have not been specific therapies or treatments preventing hematoma expansion and improve the outcome after ICH. Furthermore, it has been confirmed that neither mini-traumatic operation nor the present accessible medicine is proved to be the ideal treatment based on the available evidence-based medical researches (Morgenstern et al. 2010; Mendelow et al. 2013; Mayer et al. 2008).

Faced with the limitations of the current available therapies, herbal medicine of promoting blood circulation (PBC) and removing blood stasis (RBS) are widely and efficiently used in Chinese hospitals to treat HICH based on the TCM theory of ‘the blood flow outside the vessels is the blood stasis’. However, whether these herbal medicine can cause hematoma enlargement leading to serious adverse events is undefined until now (Li et al. 2015).

In order to evaluate the safety of PBC and RBS herbal drugs, we design a prospective, randomized, open, double-blind controlled clinical trial on the hematoma enlargement in HICH patients treating with PBC and RBS herbal medicine within 6 h time window from the symptom onset.

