### Primary outcome

The primary end-point measure is the percent change in the hematoma volume measured by ABC/2 Coniglobus formula (Kothari et al. 1996) at the 24th hour after the onset. Hematoma growth is operationally defined as an increase in the hematoma volume of >33 % as measured by image analysis on the 24 h CT compared with the baseline CT scan.

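### The logarithm planned for the primary outcome is undefined for any haematoma that shrinks or stays the same, and the article names three different variables as the one to be analysed

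*Protocol article*

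**What the plan says.** Three statements bear on which variable is analysed.

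- **Percentage change.** The Primary outcome section says: "The primary end-point measure is the percent change in the hematoma volume". The Statistical analyses section repeats it: "The primary outcome is the percent change in the volume of the hematoma measured by a CT scan at 24 ± 3 h after the onset". It then adds the transformation: "The percentages of changes in the volume of hematoma are transformed to normality and eliminate negative values via logarithmic transformations".
- **Volume.** The same section describes the model this way: "The volumes of the hematoma measured by a CT scan will be analyzed using generalized linear mixed models". Baseline volume is among the covariates.
- **Relative volume.** The Sample size section says: "Power and sample size are determined using relative hematoma volume at 24 h as the main outcome variable".

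The Statistical analyses section also commits every analysis to intention to treat and sets 0.0167 as the threshold for comparisons with placebo. The section on missing data offers multiple imputation for other incomplete primary outcome data. Nowhere does the article give a constant to be added before taking logs, or a rule for changes of zero or below.

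**The concern.** The sentence shows that negative values are expected, but the remedy it names fails on exactly those values. A logarithm needs positive input. It does not eliminate negative numbers; software returns them as missing.

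The affected patients are those whose haematoma did not grow, which is the best result on this outcome. If a herbal formula reduces growth, more of its patients have undefined values; if it promotes growth, fewer do. An analysis restricted to haematomas that grew would condition on a post-randomisation result and compare unlike subsets. The trial asks whether these medicines cause haematoma growth, so a weakened primary contrast bears on its safety conclusion as well as on efficacy.

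**Working it through.** **1. The transformation itself.** Let V0 be the baseline volume, V24 the 24 h volume, and percentage change = 100 × (V24 − V0)/V0. For changes of −20, 0 and 20, the natural log gives undefined, minus infinity and 2.996. Only the last can be analysed.

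**2. What would work.** Since 100 + percentage change = 100 × V24/V0, log(100 + percentage change) = log 100 + log(V24/V0). An offset of 100 is therefore the log ratio plus a constant, defined whenever V24 > 0. A small offset does not help: under calibration A below, adding 1 still leaves 32% of placebo and 59% of RBS values undefined.

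**3. How many patients.** The Background says: "Approximately two-third of ICH patients suffer hematoma enlargement within 24 h of ictus". *Assumption:* enlargement there means any increase. One-third then have a change of zero or below. Applied to every arm, that is 360/3 = 120 randomised or 285/3 = 95 evaluable patients; under a treatment effect the share differs by arm.

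**4. Effect of literal execution.** The article gives no figure to reproduce for the transformation, so this step is illustrative. It uses 95 per arm (285/3), log(V24/V0) normal with equal SD in all arms, and a t-test. The comparison is between the log ratio in all patients and the log of percentage change with undefined values left missing.

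*Calibration A: Table 4 (placebo 38, RBS 16, PBC 7) read as the percentage of patients growing by more than 33%.* For placebo, P(log ratio > 0) = 2/3 and P(log ratio > ln 1.33) = 0.38. So SD = ln 1.33/(0.4307 + 0.3055) = 0.2852/0.7362 = 0.387, and mean = 0.4307 × 0.387 = 0.167. The mean is then shifted to give each other proportion. Placebo has 33% undefined in every row.

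| Treated arm, share growing >33% | Undefined, treated arm | Power at 0.025: literal log / log ratio | Power at 0.0167: literal log / log ratio |
|---|---|---|---|
| 16% (RBS) | 60% | 33% / 99% | 28% / 99% |
| 7% (PBC) | 77% | 54% / 100% | 48% / 100% |
| 55% (assumed harm) | 19% | 27% / 76% | 22% / 71% |
| 38% (no difference) | 33% | 2.2% / 2.5% (type I error) | 1.4% / 1.6% (type I error) |

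The 0.025 column uses the alpha named at the start of the Statistical analyses section; the 0.0167 column uses the threshold set there for comparisons with placebo. Repeated runs gave 32% to 33% for the RBS literal-log power at 0.025, and 2.2% to 2.6% for its type I error.

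*Calibration B: Table 4 read as median percentage change,* so median V24/V0 is 1.38, 1.16 and 1.07. The SD of the log ratio is assumed; the threshold is 0.0167.

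| Assumed SD | Undefined: placebo / RBS / PBC | RBS power: literal log / log ratio | PBC power: literal log / log ratio |
|---|---|---|---|
| 0.25 | 10% / 28% / 39% | 70% / 99% | 92% / 100% |
| 0.4 | 21% / 36% / 43% | 20% / 72% | 40% / 97% |
| 0.6 | 30% / 40% / 45% | 8% / 34% | 15% / 69% |

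In every scenario with a true difference, the undefined share differs by arm and the log ratio has the higher power.

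**The case against.** The strongest reply is that the article never says anyone is excluded. It commits to intention to treat, it shows awareness of negative values, and two of its own sentences name variables that can be logged: relative volume, if read as V24/V0, and volume with baseline volume as covariate. An offset of 100 would remove the problem, and a journal article may leave such a constant to the full protocol or analysis plan.

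Much of this stands. A reader might infer that the plan removes patients without growth from the primary analysis. The documents do not support that: removal follows only if the log is applied to the raw percentage change and the undefined values are left missing. A reader might also infer that the comparison is biased towards false positives, or always loses most of its power. Neither is supported. With no difference between arms the literal analysis keeps its type I error, and at SD 0.25 under calibration B it still has 70% and 92% power.

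The magnitudes are also open to challenge. The Background does not define enlargement, whereas the trial's own definition of growth is more than 33%. Table 4 can be read in two ways, and a t-test stands in for the adjusted mixed model.

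What does not stand is the appeal to omitted detail. The article states a transformation, attaches it to the one variable on which it fails, and gives a wrong reason for it. Treating the undefined values as incomplete data would not rescue it either, because imputation would replace measured outcomes with modelled ones.

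**Conclusion.** The point holds in this form: the stated log transformation cannot be carried out for any percentage change of zero or below, and the article is inconsistent about whether percentage change, volume or relative volume is the primary variable. Literal execution would lose or impute observed outcomes differently by arm, contrary to intention to treat, with a weaker contrast and lower power for benefit or harm.

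The mathematical fault is certain; its size is not. About one-third of placebo values are affected if the Background figure means any increase. The power ranges also depend on lognormal ratios with equal SD, on the assumed SD and on the reading of Table 4. The direction was the same in every scenario examined. Because this is the primary analysis, the sentence should be corrected before unblinding.

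**What to change.** Replace the transformation sentence with: *The primary variable is log(V24/V0), analysed in the mixed model for all randomised patients, including those with no change or shrinkage; results are back-transformed to ratios of geometric means.* With log V0 as a covariate, modelling log V24 gives the same treatment estimate, so either form may be named. If a volume can be 0 ml, add one fixed small constant, set before unblinding, to both volumes. Use the same variable name in the Primary outcome, Sample size and Statistical analyses sections.

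The cost is one sentence plus consistent naming. No new data are needed, and the article reports that recruitment is still under way.

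### Testing two comparisons with placebo once each at 0.0167 leaves part of the 5% error unspent; Holm at overall 0.05 would raise approximate power for RBS vs placebo from about 86% to 94%

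*Protocol article*

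**What the plan says.** Under Statistical analyses, the primary outcome (percent change in hematoma volume at 24 h) is compared between each of the two treatment groups and placebo by Bonferroni's method "with a threshold of significance of 0.0167. The threshold of significance for all other comparisons was 0.05". No third primary comparison is named. The same section sets an alpha of 0.025 and a beta of 0.10 for all analyses, and plans a mixed model with log transformation.

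Under Sample size, the hypothesis is that "the relative hematoma volume in subjects of three groups are the same to each other". The article then states: "With a two-sided alpha level at 0.05, 285 participants finishing the final follow up provide 90 % power". Table 4 assumes 7% for PBC, 16% for RBS and 38% for placebo. Allowance for loss raises the total to 360, which is 120 per group at 1:1:1.

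Among the other outcomes, "The scores on the BI and NIHSS will be analyzed with Wilcoxon rank-sum tests". mRS has a cumulative logit model, and serious adverse events are compared across all three groups.

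**The concern.** Bonferroni over two comparisons at 5% uses 0.05/2 = 0.025 each. The plan uses 0.05/3, so some of the permitted error is never used. Single-step testing gives up more, because Holm's step-down version over the same two comparisons keeps the same 5% limit and never rejects less often than single-step 0.025.

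PBC vs placebo has power to spare on the assumed rates, so the loss falls on RBS vs placebo. That is the smaller assumed difference, and RBS is the therapy named in the Objective. At stake is an avoidable chance of missing that difference, with 280 of 360 patients already recruited when the article was written.

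**Working it through.** **Inputs.** Rates 7% / 16% / 38% (Table 4); 285 completers, so 95 per group; overall two-sided alpha 0.05 (Sample size); two comparisons, each at 0.0167, and beta 0.10 (Statistical analyses).

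**The plan's own figure.** The printed formula, in degrees, with 12.65, 38% and 7%: arcsin√0.38 = 38.06° and arcsin√0.07 = 15.34°, a difference of 22.715°. Then 1641.6 × 12.65 / 22.715² = 40.2 per group, about 121 in total. The stated 285 is not reproduced. The constant 12.65 is correct for a 2-df test at alpha 0.05 with 90% power, so the 90% refers to the three-group hypothesis. With 95 per group that overall test has about 99.9% power on the Table 4 rates. The step from 285 to 360 is consistent: 285/0.8 = 356.25, rounded up. I take 95 per group as given.

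**Error spent.** Two tests at 0.0167: at most 2 × 0.0167 = 0.0334. Simulated with all three rates at 38% (400,000 runs), the family-wise error is about 3.0% for the plan's rule and about 4.6% for Holm at 0.05.

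**Power for RBS vs placebo, arcsine scale.** h = 2 × (arcsin√0.38 − arcsin√0.16) = 2 × (0.6642 − 0.4115) = 0.505 in radians. z = h × √(95/2) = 3.48. Power = Φ(z − critical value).

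| Rule | Level for RBS vs placebo | Critical value | Power |
|---|---|---|---|
| As written | 0.0167 | 2.39 | 86.2% |
| Single-step, divisor two | 0.025 | 2.24 | 89.3% |
| Holm at the error the plan spends | 0.0334 after PBC is rejected | 2.13 | 91.2% |
| Holm at overall 0.05 | 0.05 after PBC is rejected | 1.96 | 93.6% |

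The Holm rows use the fact that PBC vs placebo is almost always rejected first: its power is at least 99.8% under every rule. Simulation agrees: 86.2% as written, 89.3% at 0.025 and 93.6% with Holm at 0.05. The pooled-variance formula gives 85.4% at 0.0167 and 88.7% at 0.025.

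**Split of the gain.** Changing the divisor first: 89.3 − 86.2 = 3.1 points from the divisor, then 93.6 − 89.3 = 4.3 from stepping down. Stepping down first, at the error the plan already spends: 91.2 − 86.2 = 5.0 points, then 93.6 − 91.2 = 2.4 from the larger error limit.

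**Sensitivity to loss.** With all 120 per group analysed, power at 0.0167 is 93.2% (pooled) to 93.6% (arcsine).

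**The case against.** Bonferroni at 0.0167 is a valid, conservative rule. The strongest reply is that 86% is not the power of the planned test. It uses binary rates in completers, whereas the plan fits a mixed model to log-transformed percent change, by intention to treat and with imputation. No standard deviation is given, so that power cannot be computed, and 95 per group is the pessimistic case. This stands for the absolute figures. It does not affect the ranking of the rules, since Holm at 0.05 rejects whenever the present rule does.

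A reader might infer three stronger points that the article does not support:

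- **That RBS vs placebo was promised 90% and gets 86%.** The 90% under Sample size belongs to the three-group hypothesis. Only the beta of 0.10 set for all analyses carries it to the pairwise tests.
- **That single-step testing alone costs 8 points at no price in error.** Part of the gain comes from the divisor, and the error limit rises from about 3.3% to 5%. At equal error the gain is about 5 points. If the divisor of three was meant to cover all three pairs, ordinary Holm would normally test RBS vs placebo at 0.025 and give about 89%. The text, however, names only two comparisons.
- **That the secondary outcomes are tested wrongly.** Rank-sum tests are named only for BI and NIHSS, and BI is not a listed secondary outcome. The pairs are not specified, so any false-positive rate per outcome would rest on an assumption. Unadjusted 0.05 for outcomes with no stated confirmatory role is common, and gating is often left to an analysis plan.

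**Conclusion.** The primary testing rule is valid but wasteful. It limits family-wise error to about 3.3% when 5% is available. On the Table 4 rates with 95 completers per group it gives RBS vs placebo about 86% power, some 4 points under the 90% implied by beta 0.10. Holm at overall 0.05 gives about 94%.

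This assumes that the family is the two named comparisons and that the overall two-sided level is the 0.05 under Sample size. The 0.025 given for all analyses has to be reconciled with that. It also assumes that the binary rates are a fair guide to the planned model. If nearly all 360 patients contribute data, power exceeds 90% even as written and the gain is smaller. Gating the NIHSS and BI tests is optional.

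**What to change.** Before the code is broken, and without knowledge of results by group, replace the 0.0167 rule with Holm on the two comparisons with placebo at overall two-sided 0.05. Test the smaller p-value against 0.025. If it is significant, test the other against 0.05; if not, stop. State in the same place that these two comparisons are the whole primary family, and align the general alpha of 0.025 with this.

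The cost is a few sentences of wording and no patients. The price is the higher error limit (5% instead of about 3.3%) and the lack of simple simultaneous confidence intervals. If such intervals matter more for the question of hematoma growth, single-step 0.025 keeps them and still recovers about 3 points.

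Optionally, state which pairs the NIHSS and BI rank-sum tests compare, and whether a three-group test comes first.
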